#### Cognitive behavioural therapy (CBT)

The CBT group is also manualised and follows the treatment plan of classical cognitive-behavioural therapy. It combines the psychoeducational parts of Schaub et al. [38] with specific exercises as well as elements of the strategic behavioural therapy (SBT) by Sulz [39] and elements of the short-term concept by Hautzinger & Kischkel [40]. At the beginning and end of each session, mindfulness-based techniques and relaxation methods are integrated. Comparable to the BPT, the CBT intervention consists of 10 consecutive sessions of 2 hours, takingplace once a week in the late afternoon in a group of about 10 patients with teams of two therapists in each study region (all in all, eight different therapists). Comparable to the qualification of the BPT therapists, all CBT therapists are either psychotherapists or psychologists who are completing their psychotherapy hours and are experienced in the treatment of depression. Prior to the intervention, all of the therapists are thoroughly trained in the implementation of the CBT manual by two members of the study’s headquarters. Similar to the BPT intervention, each of the 10 sessions focuses on a specific psychological topic (see Table 3).

**Table 3 Tab3:** Overview of the cognitive behavioural therapy sessions

Session	Topic
1	Introduction to CBT therapy and psychoeducation
2	Psychoeducation on depression and dysfunctional beliefs
3	Identifying and working on individual dysfunctional beliefs
4	Behavioural activation/ activity scheduling
5	Social relationships I
6	Social relationships II
7	Cognitive techniques I
8	Cognitive techniques II
9	Lessons learned: Transforming dysfunctional beliefs
10	Reflecting on lessons learned and on transferring them to daily life

Therapists in all of the three therapy centres follow a manual including a fixed schedule for each session. Each session consists of three main parts – comparable to the BPT manual: a) introduction – which consists of a mindfulness exercise, a short interactive repetition of the last session, and a review of the home-based exercises; b) main part – in which the specific topic is interactively developed using flipcharts, exercise sheets, and small-group work; and c) closure – where worksheets are handed out, home-based exercises are discussed, and a relaxation exercise (progressive muscle relaxation according to Jacobsen) [41] is carried out.

#### Exercise program (EP)

The home-based Exercise Program consists of a 20-min physical training program, which addresses the same muscles used in bouldering or climbing. At the beginning of the intervention, all participants receive a training manual (including instructions and explanations of all of the exercises), a training DVD, training material (e.g. a multifunctional latex band and training rings to enhance finger and underarm power), as well as psychoeducational material explaining the link between physical activity and mood. Participants are instructed to engage in the training program on their own at home approximately three times a week for the study period of 10 weeks. They receive reminders via e-mail to motivate them to keep on exercising. At the midpoint of the intervention (5 weeks), they are sent additional motivational material via postal mail. After 10 weeks, participants are asked how often they conducted the exercises. After the second measurement point, former EP participants are offered the opportunity to participate in a subsequent 10-week bouldering group, which follows the same treatment plan as the BPT group.

### Data collection

The collection of the outcome data is being conducted via CATIs with the patients. The data are being collected before the beginning of the intervention (t0), at the end of the 10-week intervention period (t1), and 3 months (t2), 6 months (t3), and 12 months (t4) after the end of the intervention period. To prepare patients for the interview, they are sent the questionnaire a few days before the interview takes place. The CATI interviewers are clinical psychology students who are trained at the study’s headquarters.

### Measures

The measures employed at the different measurement points are shown in Fig. 1.

#### Primary outcome measures

*Montgomery-Asberg Depression Rating Scale (MADRS)* [42]. The MADRS is one of the most commonly used rating scales for assessing the core symptoms of depression [43]. It is conducted as a semi-structured clinician-rated interview consisting of 10 items: apparent sadness, reported sadness, inner tension, reduced sleep, reduced appetite, concentration difficulties, lassitude, inability to feel, pessimistic thoughts, and suicidal thoughts. The items ask patients about their experiences during the last week. Each item is rated on a seven-point scale from zero to six with higher scores indicating greater severity of symptoms. A score greater than 31 on the MADRS indicates severe depression, whereas a score of 10 or below indicates remission [44, 45]. The interrater reliability is high and it is sensitive to change [42]. Originally, the scale was published without wording suggestions for clinicians to help them collect the information required to rate the items. For this reason, we used the *structured interview guide for the Montgomery-Asberg Depression Rating Scale (SIGMA)* [43]. The SIGMA is a structured interview guide that offers a selection of different questions for each of the 10 items with good to excellent interrater reliabilities [43].

*The 9-Item Patient Health Questionnaire (PHQ-9)* [46, 47]. The PHQ-9 is a short self-assessment tool often used in primary care settings to screen for depression [48]. Its nine items cover the nine DSM-IV criteria and are rated on a four-point scale ranging from zero (“not at all”) to three (“nearly every day”). The items ask patients about their experiences during the last 2 weeks. The total sum score suggests varying levels of depression. Scores from 0 to 4 indicate minimal depression, scores from 5 to 9 mild depression, scores from 10 to 14 moderate depression, scores from 15 to 19 moderately severe depression, and scores from 20 to 27 severe depression [37, 46]. In the German validation study of the PHQ-9 a cut-off point of 8 had the best relation of sensitivity and specifity [37]. The PHQ-9 is well validated and sensitive to change [49].

#### Secondary outcome measures

*EuroQol Five Dimension Questionnaire (EQ-5D)* visual analogue scale *(VAS)* [50]. The EQ-5D assesses health-related quality of life. For the purpose of this study, we included the VAS to ask patients to rate how good or bad their health-related quality of life (HRQoL) is today. The scale is numbered from zero (“worst HRQoL”) to 100 (“best HRQoL”). It was found to be practicable and useful for the application in the general population [51].

*Questionnaire on Resources and Self-Management Skills (Fragebogen zur Erfassung von Ressourcen und Selbstmanagementfähigkeiten, FERUS)* [52]*.* The FERUS assesses individuals’ health-related resources and manageability. It consists of seven scales, but we included only the *coping* subscale with 12 items. Items are rated on a five-point Likert scale that ranges from one to five, with higher test scores indicating good coping skills. All scales of the FERUS have high convergent and discriminant validities and the retest reliabilities are good to satisfying [52, 53].

*Body Image Questionnaire (Fragebogen zum Körperbild, FKB-20)* [54]. The FKB-20 assesses body image disturbances and subjective aspects of body experience. It consists of two subscales of 10 items each. For the purpose of this study, we included only the *vital body dynamics* subscale. Each item is rated on a five-point scale ranging from one (“strongly disagree”) to five (“strongly agree”) with higher values indicating a more positive body image. The statistical properties proved to be satisfying [55].

*Generalized Anxiety Disorder 7 (GAD-7)* [47, 56]. The GAD-7 is a brief self-reported questionnaire for assessing generalized anxiety disorder. Patients are asked how often they have felt bothered by each of the seven core symptoms of generalized anxiety disorder during the last 2 weeks. Items can be rated on a four-point scale ranging from zero (“not at all”) to three (“nearly every day”). Scores range from zero to 21, with scores of ≥5, ≥ 10, and ≥ 15 indicating mild, moderate, and severe anxiety symptoms, respectively. The GAD-7 proved to be a reliable and valid instrument [56].

*General Self-Efficacy Scale (GSE)* [57]. The GSE measures optimistic self-beliefs about coping with a variety of difficult demands in life. Its 10 items can be rated on a four-point scale ranging from one (“not at all true”) to four (“exactly true”). The total score ranges from 10 to 40 with higher scores indicating higher self-efficacy. The GSE has good psychometric properties [58].

*Rosenberg Self-Esteem Scale (R-SES)* [53, 59]. The R-SES is a self-report instrument for evaluating global self-worth by measuring both positive and negative feelings about the self. Its 10 items can be answered on a four-point scale ranging from zero (“strongly disagree”) to three (“strongly agree”) with higher values indicating stronger self-esteem. The psychometric properties of the scale are satisfactory [60].

*Symptom-Checklist (SCL-90)*. The SCL-90 is a self-report inventory that is used to examine the global intensity of psychological symptoms and distress experienced during the past 7 days using a five-point Likert-type scale ranging from zero to four. The SCL-90 covers nine symptom dimensions, but for the purposes of this study, we used only the *interpersonal sensitivity* subscale. Ratings are summed for each subscale with higher scores indicating greater severity of symptoms. The SCL-90 is a reliable instrument and has satisfying convergent and discriminant validities [61].

#### Other measures

##### Screening questionnaire

The screening questionnaire is filled out by individuals interested in participating in the study after attending the informational sessions for the purpose of assessing the inclusion and exclusion criteria. It consists of sociodemographic data such as age and gender as well as open questions that reflect the criteria for inclusion and exclusion (e.g. height and weight to calculate BMI, current therapeutic treatment, physical limitations, psychiatric comorbidities, and depressive symptoms as assessed with the PHQ-9).

The following data are being assessed via the CATIs in addition to the questionnaires presented above*:*

*Sociodemographic data* (e.g. family status, level of education).

Data regarding *current occupation* (e.g. ability to work, current sick-leave status).

*Medical history regarding depression* (onset, duration, and progression of depression).

*Current therapeutic treatment* (medical, psychological, and drug treatment as well as inpatient treatment).

*Critical life events* during the past 6 months (e.g. death of a relative).

*Physical activity* (frequency and kind of activity beyond activities included in the study).

*Attitude towards physical activity* (positive or negative attitude).

*Attitude towards future group allocation* (EP, CBT, BPT, comfortable, uncomfortable, no preference)

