**Discussion:**

This is the first study to investigate the effect of a bouldering psychotherapy (BPT) on outpatients’ depressive symptoms compared with mere physical activity (superiority analysis) and state-of-the-art cognitive behavioural therapy (CBT, non-inferiority analysis).

Methodological strengths of the study are the elaborated, multicentred, randomised, controlled design. Assessors are blinded with regard to group allocation which leads to high objectivity. The study is conducted in a naturalistic setting, which leads to high external validity. Methodological limitations might be the clinical heterogeneity of the sample, which may dilute the intervention effects.

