#### Masking

Participants know which treatment condition they are in, but the interviewers who conduct the CATIs and thus assess the outcomes of the study are blinded to participants’ allocations. Prior to each interview, all participants are reminded of the confidential nature of their allocation and asked not to tell the interviewer which treatment they receive.

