### Data quality management

All of the therapists and interviewers involved in the study are thoroughly trained for their respective tasks at the study’s headquarters. Therapists and interviewers constantly remain in close contact with the study’s headquarters and discuss all upcoming questions and therapeutic progress in regular appointments. For questions or to eliminate uncertainties, the study headquarters’ staff can be contacted anytime during the entire study period. Treatment adherence is documented in protocol assessment surveys, which are filled out by the therapists after each session (e.g. deviations from the manual, severe adverse events, and other extraordinary events). To obtain evidence of the inter-rater reliability of the SIGMA, 5% of the pre- (t0) and 5% of the post- (t1) intervention data are being collected with the participation of a second person who is observing. The quality of the data is guaranteed by strict data monitoring at the study’s headquarters over the entire period of data collection.

The patient information sheet contains a data protection declaration that is in accordance with European and German data protection laws. Sensitive data collected during the telephone interviews is pseudonymised and stored in password-protected devices. Names and addresses of the participants are recorded separately and password-protected. Patient information sheets and the screening questionnaires are stored in a locked steel cabinet. Only members of the study team have access to the lists of the names and codes of participants. No published material will contain patient identifying information.

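### Assessor blinding of the MADRS is put at risk, though not shown to be broken, by an unrestricted treatment question in the rating interview and by interviewers' appointments on therapeutic progress

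*Protocol article*

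**What the plan says.** Under Masking, the protocol article states that "the interviewers who conduct the CATIs and thus assess the outcomes of the study are blinded" to allocation. The safeguard it names is that before each interview "all participants are reminded of the confidential nature of their allocation and asked not to tell the interviewer which treatment they receive". The abstract draws a strength from this: "Assessors are blinded with regard to group allocation which leads to high objectivity". The main Discussion repeats the argument.

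The outcome protected by this blinding depends on a rater. Under Primary outcome measures, the article says of the MADRS: "It is conducted as a semi-structured clinician-rated interview consisting of 10 items". The Data collection section says that the raters are trained psychology students.

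Four other parts of the article bear on what these raters may learn:

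- **Other measures, list of further interview items.** The telephone interviews also cover current treatment of every kind, psychological treatment included. No written limit keeps the study therapy out of the answer. The physical-activity item does carry such a limit: "frequency and kind of activity beyond activities included in the study".
- **Data quality management.** Therapists and interviewers are together the subject of a sentence saying that they keep in touch with headquarters and "discuss all upcoming questions and therapeutic progress in regular appointments".
- **Exercise program (EP).** "After 10 weeks, participants are asked how often they conducted the exercises". The article does not say who asks.
- **Table 1.** Recruitment status is given as complete.

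**The concern.** Participants and therapists cannot be blinded here, so protection against detection bias in the MADRS rests on the interviewer not knowing the arm. That in turn rests largely on participants remembering a request. An interview that then asks an open question about current psychological treatment invites a BPT or CBT participant who answers truthfully to mention the weekly group. Appointments in which raters discuss therapeutic progress open a second route by which allocation could reach them.

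The MADRS directly after the intervention is the primary outcome. It carries the superiority test of BPT against EP and one part of the non-inferiority test of BPT against CBT. A rater who has learned the arm before or during the rating may score differently. The smallest MADRS margin is narrow, at half of d = 0.4, so even a modest difference in rating between arms would matter.

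**Working it through.** The article gives no disclosure rate, no check on guessed allocation and no estimate of bias, so there is no figure of its own to reproduce. The check is a comparison of its statements, followed by an illustration of scale.

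**Step 1: what each procedure can reveal.**

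| Procedure | Could it reveal the arm? | What the article settles |
|---|---|---|
| Current-treatment item | Yes, if the participant counts the study group as psychological treatment | Collected in the same interviews as the outcomes; no written exclusion of study therapy |
| Physical-activity item | Only by a slip, since study activity is excluded by its wording | Limit stated |
| Appointments on therapeutic progress | Yes, if arm or individual patients come up | Interviewers are named as taking part; whether they meet therapists jointly is not said |
| EP exercise-frequency question | Yes, if the blinded interviewer asks it | Timing matches t1; the asker is not named and the question is not in the list of interview items |

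Two rows conflict with Masking on the wording itself: the treatment item and the appointments. The other two add risk only under a further condition.

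**Step 2: is the treatment item asked at t1?** The schedule is in Fig. 1, which is not available here, so this cannot be confirmed. It is the natural reading. The Hypothesis I section plans to adjust for treatment used outside the study, and the Discussion lets participants start additional treatment while in the study. A question asked only at baseline would miss treatment started later.

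**Step 3: scale (illustration only).** Inputs from the article: ten items scored 0 to 6, so a range of 10 × 6 = 60 points, and margins of d = 0.20 and 0.34. Assumed, because the article gives no SD for the MADRS: SD 7 to 9.

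- Margin in points = d × SD.
- For d = 0.20: 0.20 × 7 = 1.4 and 0.20 × 9 = 1.8.
- For d = 0.34: 0.34 × 7 = 2.38 and 0.34 × 9 = 3.06.

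The shift in an arm's mean is the disclosure rate times the rating shift in disclosed interviews. Suppose the shift is 2 points (one point on each of two items) and occurs in one arm only:

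| Disclosure rate (assumed) | Mean shift | Share of the 1.8 to 1.4-point margin |
|---|---|---|
| 20% | 0.20 × 2 = 0.4 | 22% to 29% |
| 50% | 0.50 × 2 = 1.0 | 56% to 71% |
| 100% | 1.00 × 2 = 2.0 | 111% to 143% |

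To equal the smallest margin, a 2-point shift would need a disclosure rate of 1.4 / 2 = 70% to 1.8 / 2 = 90% in one arm and no shift in the other. If both arms are affected alike, the shifts cancel in the comparison.

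**The case against.** The strongest defence is that nothing in the article says a rater learns the arm.

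- **The activity item is worded to keep study exercise out.** This stands. A reader might infer that the item reveals the arm; its wording points the other way, and at most it may prompt an accidental remark.
- **The treatment data are meant for care outside the study.** The Hypothesis I section supports this as the intention. It does not tell the participant what to leave out, and the limit written into the activity item is absent from the treatment item.
- **The appointments may be separate.** This stands as a possible reading: interviewers may raise their questions while therapists report progress. A reader might infer that raters sit with therapists and hear about named patients, which is not stated. Even so, the sentence has interviewers discussing progress and states no separation.
- **The EP question may be asked by headquarters,** which supervises that arm. This also stands, so the question counts only conditionally.
- **Other safeguards exist.** The structured interview guide (SIGMA) limits rater discretion. The second observer in 5% of interviews at t0 and 5% at t1 gives evidence on agreement, but hears the same conversation and so would not expose an effect of disclosure.
- **Hypothesis II is also tested on the PHQ-9,** a self-report scale that was the basis of its sample size. This narrows the exposure of Hypothesis II. It does not help Hypothesis I, whose outcome is the MADRS.
- **Interview order is operating detail that an article may omit.** This is fair for the order alone, and the MADRS may already come first. The point here rests on what the article does state, which sits badly with its blinding claim.

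**Conclusion.** The blinding is at risk from two stated procedures, the unrestricted treatment item and the appointments on therapeutic progress. It is not shown to have failed. The EP adherence question would add to the risk only if the blinded interviewer asks it.

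Three stronger conclusions are tempting and are not supported:

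- **That any bias favours BPT.** The article gives no basis for a direction.
- **That its size reaches the non-inferiority margin.** That needs near-complete, one-sided disclosure with a consistent 2-point shift, and both the shift and the SD of 7 to 9 are assumptions.
- **That EP participants who join the bouldering group later compromise the primary result.** That offer comes after t1, so it can touch only the ratings at t2 to t4.

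The disclosure rate is unknown, and the article describes no record from which it could be learned. The point is worth acting on because the primary outcome is interviewer-rated and the remedy costs little. The sections on Masking, Other measures, Exercise program and Data quality management should be reconciled.

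**What to change.** 1. Complete and lock the MADRS (SIGMA) before the items on treatment and physical activity, and word the treatment item so that it excludes study treatment.
2. Have headquarters staff who do not rate outcomes collect the EP exercise frequency, and say so.
3. Limit interviewers' appointments to rating questions, with no information on therapy progress or arm.
4. Have the interviewer record, directly after the MADRS, whether the arm was disclosed. Report the disclosure rate by arm, and repeat the t1 MADRS comparisons without the disclosed interviews as a sensitivity analysis. Because disclosure happens after randomisation and may differ by arm, this analysis supports the main one and does not replace it.
5. For interviews already done, state that the disclosure rate is unknown and qualify the claim of high objectivity in the abstract and Discussion.

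The cost is a reordered script, one reworded item, one tick-box and separate appointments, with no extra visits. The downside is that question order would differ between waves. With recruitment listed as complete, many t1 interviews may be past correction; for those only the fifth step applies.

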##### Avoidance behaviour

On a self-developed five-point scale ranging from zero (“not at all”) to four (“extremely”), we ask patients whether and how much they avoid certain places, public transportation, special situations, or other.

### Data quality management

All of the therapists and interviewers involved in the study are thoroughly trained for their respective tasks at the study’s headquarters. Therapists and interviewers constantly remain in close contact with the study’s headquarters and discuss all upcoming questions and therapeutic progress in regular appointments. For questions or to eliminate uncertainties, the study headquarters’ staff can be contacted anytime during the entire study period. Treatment adherence is documented in protocol assessment surveys, which are filled out by the therapists after each session (e.g. deviations from the manual, severe adverse events, and other extraordinary events). To obtain evidence of the inter-rater reliability of the SIGMA, 5% of the pre- (t0) and 5% of the post- (t1) intervention data are being collected with the participation of a second person who is observing. The quality of the data is guaranteed by strict data monitoring at the study’s headquarters over the entire period of data collection.

The patient information sheet contains a data protection declaration that is in accordance with European and German data protection laws. Sensitive data collected during the telephone interviews is pseudonymised and stored in password-protected devices. Names and addresses of the participants are recorded separately and password-protected. Patient information sheets and the screening questionnaires are stored in a locked steel cabinet. Only members of the study team have access to the lists of the names and codes of participants. No published material will contain patient identifying information.

